### Treatment

All patients included in the study will use the study medication in addition to their current antipsychotic medication as prescribed by their treating physician at the time of inclusion. Study medication kits were prepared by ACE Pharmaceuticals (The Netherlands and Belgium) and Kragerø Tablettproduksjon AS (Norway). They were provided with a randomization list indicating which kit number should contain which treatment. The pharmaceutical company responsible for manufacturing the study medication ensured that the tablets are indistinguishable in appearance, shape, smell, mass, and taste.

Study medication will be tapered-off within 6 weeks in the following schedule: 40 mg/day for 3 days and 30 mg/day for 4 days, followed by a decrease of 5 mg/day per week during the remaining 5 weeks; in the second week, patients will use 25 mg/day, in the third week 20 mg/day, etc. In the last week the patients will only take prednisolone on days 1–3 and day 5 and 7; a tapering scheme in line with the treatment guidelines for inflammatory bowel diseases (2008). Each study medication kit consists of six weekly boxes, each containing all dosages for one week, in which the study medication tablets are sorted according to the tapering-off schedule. Each weekly box is labeled in line with Annex 13 of Clinical Trial Directive.

To prevent loss of bone mass, we will provide calcium supplementation (calciumcarbonate 500 mg daily) and vitamin D supplementation (cholecalciferol 400 IU daily). Pantroprazole will be actively provided to patients with a history of ventricular/duodenal ulcer.

### Outcome variables

#### Primary outcome variables

##### Clinical outcome measure

Our main study parameter is overall symptom severity as measured with the PANSS total score.

#### Secondary outcome variables

##### Symptom severity

Secondary study parameters include PANSS total scores 4, 6, and 12 months after start of the treatment. Furthermore, general functioning will be evaluated using the GAF comparing patients treated with prednisolone versus placebo.

##### Cognitive assessment

Neurocognitive functioning as measured with the BACS will be used to measure the possible improvement over the treatment and the 6-month follow-up period. The BACS was chosen as the neurocognitive measure due to its repeatability as well as the short assessment time (35 min), which is expected to lead to higher completion rates and fewer missing data. The BACS has been developed for assessing the domains of cognitive functioning in schizophrenia trials [43]. It consists of the following domains:
Verbal memory: List LearningWorking memory: Digit Sequencing TaskMotor speed: Token Motor TaskVerbal fluency: Category InstancesVerbal fluency: Controlled Oral Word Association TestAttention and speed of information processing: Symbol CodingExecutive functions: Tower of London

##### Laboratory assessments

Immunological and metabolic parameters will be assessed four times over the 1-year study period. We will investigate inflammatory processes that may be involved in a subpopulation of patients with psychotic disorders using prednisolone augmentation [33]. To investigate immunological biomarkers that predict treatment response to prednisolone therapy, we will collect serum and RNA of all patients at baseline and 3, 6, and 26 weeks after the start of the study medication use. The laboratory assessments will contain the following analyses:
Multiplex immunoassayInfectious disease profilingFlow cytometrySelective reaction monitoring (SRM)

##### Brain imaging (optional in Norway)

Information regarding the brain imaging part of the study conducted in Norway can be found in Additional file 2.

#### Other objectives

Severity of depression will be assessed and compared between groups using the CDS. The need to adjust current antipsychotic medication by 25% or more is compared between groups. Finally, safety data will be assessed by comparing incidence (number and percentage of subjects with at least one occurrence) of key SAEs and suspected unexpected serious adverse reactions (SUSARs) between both groups, e.g., hospitalizations.

### Safety assessment

#### Safety measurements

At each visit a study physician (psychiatrist or psychiatry resident) will review the possible adverse events (especially neuropsychiatric side effects), medication use, and any contraindications for prednisolone use. After the screening visit, the blood results will be reviewed by a study physician regarding the inclusion and exclusion criteria. After the baseline visit at which patients start study medication, safety parameters will be checked by a study physician who is not conducting any other protocol assessment. Based on blood assessment, presence of adverse events, and contraindications for prednisolone use, it will be determined if it is still safe to use the study medication.

#### Stopping rules

Several events that may jeopardize the patient’s health will prompt clinicians to end the study and start tapering the patient off the study medication immediately in line with the treatment guidelines for inflammatory bowel diseases (2008). These events include the patient developing:
A (fasting) blood glucose exceeding 7.0 mmol/L; in case a non-fasting glucose level was determined, a blood glucose level exceeding 11 mmol/LSuicidal ideations assessed by the CDS, the following cut-off are applicable based on item 8: Suicidal ideations within the CDS
◦ Score of 0: no action (no suicidal ideation)◦ Score of 1: consult with clinician (passive suicidal ideation)◦ Score of 2/3: potential cause to stop study medication treatment—consult with clinician (active suicidal ideation)A PANSS positive subscore which increases by 10 or more points without a clear reason (i.e., medication non-adherence)PANSS item G6 (depression) exceeding a score of 4The need for coercive treatmentPregnancyOral systematic infectious disease

#### Adverse events

Any undesirable experience occurring in a subject during the study is defined as an adverse event (AE), regardless of any relatedness to the study medication. All AEs reported spontaneously by the subject or observed by the investigator or study team members conducting the visit will be recorded. AEs will be checked by a study physician every visit by asking an open question about how the patient is doing and if the patient was suffering from any AE. Furthermore, the study physician will assess a standardized questionnaire which includes all potential prednisolone-related AEs. If an AE requires follow-up, the study physician will inform the general practitioner, will examine and monitor the AE him/herself, or, if necessary, will liaise with a medical specialist. In case SAEs have occurred, the applicable authorities will be informed as described in the study protocol following the guidelines. In line with local laws and regulations, participant insurance is in place in case any harm caused by the trial procedures is experienced by the participants.

### Power calculation and statistical analysis

A two group *t*-test with a 0.050 two-sided significance level will have 80% power to detect an effect size of 0.610 when the sample sizes in the two groups are 44 and 44, respectively (a total sample size of 88; text generated by nQuery Advisor). Subsequently, the sample size can be reduced by the data with an Ancova instead of analyzing a *t*-test [46]. The level of reduction depends on the correlation (r) between baseline and follow up measurements: N-ANCOVA = ((1 − r2) × N *t*-test) + 1. From a previous study in this hospital (OPTiMiSE trial) where a PANSS was performed at baseline and after 6 weeks, r = 0.48 was found. Therefore, N-ANCOVA = ((1 − 0.482) × 88) + 1 = 68.7248. Lastly, we expect a considerable number of drop outs. Assuming a drop-out rate of 30%, the definitive sample size is calculated at 68.7248 × 1.3 = 89.34224, which makes a total of *N* = 90 patients.

Statistical analyses for baseline characteristics and the outcomes regarding symptom severity, global functioning, depressive symptoms, and cognition will be performed in IBM SPSS Statistics version 25.0 [47]. A summary of the baseline characteristics will be created in order to assess baseline differences across the treatment groups. Normal distributed data will be expressed as means and standard deviations, and categorical data will be expressed as percentages. The baseline characteristics of the prednisolone and placebo group will be compared and tested with a *t*-test (for continuous variables) and a Chi-square test (for categorical variables). In this study we will use a mixed model analysis. Since we do not estimate a linear change in this analysis, the increase in efficiency compared to the analysis of covariance and therefore the reduction in sample size will not be immense and this calculation will suffice. The mixed model analysis will allow us to use the data of the discontinued patients as it takes into account all observations. This analysis will be used for the objectives regarding symptom severity, global functioning, depressive symptoms, cognition, and MRI. As stratification was performed for gender, center, and country, these variables will be used as covariates in the analyses in addition to variables that are significantly different between treatment groups as well as the unused pills (percentage over the whole treatment period) to take into account compliance with study medication.

Statistical analysis for the prediction of treatment response to prednisolone therapy using immune markers will be conducted using R software. Protein concentrations before and after treatment with prednisolone and placebo will be compared using mixed effects analysis of covariance adjusted for covariates significantly differing between the groups. Association of clinical outcomes with baseline levels of selected biomarkers in the prednisolone treatment group (i.e., prediction of treatment response) will be assessed using fixed effects analysis of covariance with adjustment for significant covariates. Sensitivity analyses will be conducted by excluding covariates from the analysis of covariance models and, if applicable, including outliers.

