#### Allocation

All 90 patients will be randomized 1:1 to either prednisolone or placebo for 6 weeks study medication use, in addition to their current antipsychotic medication as prescribed by their treating physician. A randomization list has been created independently by the data management team of the Julius Center, University Medical Center, Utrecht (The Netherlands and Belgium) and by biostatisticians at the University of Bergen, Bergen (Norway). Study medication kits were manufactured based on this randomization list. A web-based application (*https://www.juliuscentrum.nl/random/* in the Netherlands and Belgium) and a paper randomization list are used by blinded study team members to allocate the applicable kit number to each patient. Randomization was stratified for country, center, and gender.

The study staff will not have access to the trial treatment randomization codes. These will be stored in the pharmacy in the University Medical Center Utrecht (The Netherlands), Ziekenhuis Netwerk Antwerpen (Belgium), and Haukeland University Hospital (Norway) in case emergency unblinding is needed. In the case of serious adverse events (SAEs) where knowledge regarding the assigned treatment is important to decide on medical management of the emergency event, unblinding is permitted.

This study is a double-blind placebo controlled trial in which both the patients and the study team members are blind to treatment allocation. None of the study team members have access to the randomization codes. The study physicians who are reviewing laboratory reports for safety purposes are prohibited from collecting any study data for those individual patients. The laboratory results are stored in a location which is not accessible to the study team members conducting protocol procedures.

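### The 30% drop-out allowance is applied as × 1.3 instead of ÷ 0.7, so 90 patients cover only about 23% drop-out on the protocol's own calculation

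*Protocol article*

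**What the plan says.** All of the calculation stands in the protocol article under Power calculation and statistical analysis. It has three steps.

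1. A t-test comparison at the two-sided 5% level, which "will have 80% power to detect an effect size of 0.610". This step takes 44 patients per arm, 88 in all.
2. A reduction for ANCOVA, N = (1 − r²) × 88 + 1, with r taken from an earlier trial "where a PANSS was performed at baseline and after 6 weeks, r = 0.48 was found". The result is 68.7248.
3. An allowance for drop-out: "Assuming a drop-out rate of 30%, the definitive sample size is calculated at 68.7248 × 1.3 = 89.34224", rounded up to 90.

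The Allocation section carries this figure forward: "All 90 patients will be randomized 1:1 to either prednisolone or placebo".

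The same sample-size section names a mixed model as the analysis. Of its efficiency relative to ANCOVA it says that "the reduction in sample size will not be immense and this calculation will suffice". It then adds a separate advantage: the model can draw on whatever scores patients provided before they discontinued.

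**The concern.** A drop-out rate is a fraction of the patients randomised. To keep 68.7 patients after losing 30% of those who start, the required number must be divided by 1 − 0.30. Multiplying by 1.3 adds 30% of the completers, which is a smaller number of patients. The size of 90 therefore does not follow from the protocol's own inputs.

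At stake is the only justification given for the trial's size. The authors expect many drop-outs, and the Discussion says that a negative result would lower their interest in testing other anti-inflammatory drugs as add-on treatment. A reader of a null result needs to know what power the trial had at the drop-out rate it assumed.

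**Working it through.** **Inputs** (all from Power calculation and statistical analysis, except the allocation ratio, from Allocation): two-sided α = 0.05; power 80%; standardised effect d = 0.610; 44 per group by t-test; r = 0.48; drop-out 30%; 1:1 allocation; N = 90.

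**Step 1: reproduce the protocol's figures.**
- t-test, 44 per group, d = 0.610, non-central t: power 80.8%. Agrees.
- ANCOVA: (1 − 0.48²) × 88 + 1 = 0.7696 × 88 + 1 = 68.7248. Agrees.
- Inflation as printed: 68.7248 × 1.3 = 89.34, rounded to 90. Agrees.

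The multiplication is carried out correctly. The factor is what is wrong.

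**Step 2: apply a 30% loss.**
- Required number: 68.7248 / (1 − 0.30) = 98.2, so 99, or 100 for equal arms.
- Forward check: 90 × 0.70 = 63 completers, against 69 needed. By contrast 99 × 0.70 = 69.3.
- Drop-out that 90 can absorb: 1 − 68.7248/90 = 23.6%, or 1 − 69/90 = 23.3% with whole patients.

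**Step 3: power with completers only.** Adjusting for baseline turns d into 0.61/√(1 − 0.48²) = 0.695. The non-centrality is 0.695 × √(N/4), with N − 3 degrees of freedom.

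| Completers | Drop-out from 90 | ANCOVA power, d = 0.61 |
|---|---|---|
| 63 | 30.0% | 77.5% |
| 66 | 26.7% | 79.4% |
| 67 | 25.6% | 80.0% |
| 69 | 23.3% | 81.2% |

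A normal approximation gives 78.8% at 63. The effect detectable with 80% power at 63 completers is about 0.63.

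Two thresholds must be kept apart. Meeting the formula's 69 allows drop-out up to about 23%. Reaching 80% power needs 67 completers, so it allows up to about 25%. They differ because 44 per group and the ANCOVA formula leave a little slack above 80%.

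**Step 4: what the mixed model could recover.** The protocol gives no correlations between post-baseline visits, so these are assumptions. Suppose the 27 drop-outs leave evenly: 9 before week 2, 9 after week 2 and 9 after week 4. Table 1 schedules the PANSS at weeks 2, 4 and 6. The information on the week-6 contrast is summed over these patterns, for adjacent-visit correlations (given baseline) of 0.5 to 0.85. The week-2 to week-6 correlation is either the square of the adjacent one (decaying) or equal to it (constant).

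| Adjacent-visit correlation | Effective N (decaying to constant) | Power |
|---|---|---|
| 0.5 | 65.4 to 67.4 | 79.1% to 80.3% |
| 0.6 | 66.9 to 69.3 | 79.9% to 81.4% |
| 0.7 | 68.8 to 71.6 | 81.1% to 82.6% |
| 0.8 | 71.6 to 74.2 | 82.6% to 84.0% |
| 0.85 | 73.3 to 75.7 | 83.6% to 84.7% |

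The range is about 79% to 85%.

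**The case against.** The strongest reply is that completers-only ANCOVA is not the planned analysis. The mixed model uses whatever PANSS scores a discontinued patient has, and Table 1 also schedules a PANSS at an early termination visit. Only 2.5 points of power are missing on the completer basis, so a small gain is enough. The remark that the efficiency gain over ANCOVA is limited concerns the possible reduction in sample size; retention of drop-outs' data is given separately as a benefit.

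This stands as far as power goes. A reader might infer from the shortfall of six completers that the trial does not deliver 80% power, or that 80% power and 30% drop-out cannot both hold with 90 patients. The documents do not support that. It is true of a completers-only ANCOVA, but under plausible correlations the planned analysis comes out close to or above 80%.

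The reply does not rescue the printed calculation. The protocol does not use the mixed model to justify 90: it keeps the ANCOVA calculation as sufficient. Inflating for drop-out treats those patients as lost, and the inflation uses the wrong factor. The recovery also depends on correlations that the protocol does not state, and at the low end of the assumed range it falls just short of 80%.

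**Conclusion.** The inflation step is wrong as printed: a 30% loss requires 99 patients, and 90 leaves 63 completers where the formula asks for 69. This follows from the protocol's own inputs and needs no outside assumption.

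The consequence is modest. If drop-outs are treated as lost, power falls to about 77.5% and the detectable effect rises from 0.61 to about 0.63. Whether the planned analysis falls below 80% cannot be settled from the document. It depends on the visit correlations and on when patients leave. The 79–85% range assumes that drop-out is spread evenly over visits and that the missing scores are predictable from the observed ones. This is a correction to the stated figures and should be made, but it is not a failure of the design.

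**What to change.** Keep N = 90 and correct the sample-size paragraph:

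- Replace the last step by 68.7248/(1 − 0.30) = 98.2.
- State that 90 randomised patients meet the formula's 69 only if drop-out is at most about 23%, and that 80% power in a completer ANCOVA needs 67 completers (drop-out up to about 25%).
- State that at 30% drop-out (63 completers) completer ANCOVA power is about 77% for an effect size of 0.61, with a detectable effect of about 0.63.
- If the mixed model is relied on to make up the difference, give that calculation with its assumed visit correlations and drop-out pattern.

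The cost is a reworded paragraph and a slightly less favourable power statement. No extra patients and no change of analysis are needed. This suits a trial whose Dutch and Belgian recruitment, according to Trial status, was already complete.

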**Methods/design:**

In total, 90 subjects aged 18–70 years and diagnosed with schizophrenia, schizoaffective disorder, or schizophreniform disorder (Diagnostic and Statistical Manual of Mental Disorders-IV (DSM-IV) 295.x) or psychosis not otherwise specified (NOS; 298.9) will be included. The time interval between the onset of psychosis and study entry should not exceed 7 years. Patients will be randomized 1:1 to either prednisolone or placebo daily for a period of 6 weeks in addition to a stable dose of antipsychotic medication. Study medication will be initiated at 40 mg for 3 days, after which it will be tapered down within 6 weeks after initiation, following inflammatory bowel diseases treatment guidelines. Primary outcome is change in symptom severity, expressed as change in total score on the Positive and Negative Symptom Scale (PANSS) from baseline to end of treatment. Cognitive functioning (measured through the Brief Assessment of Cognition in Schizophrenia (BACS)) and change in Global Assessment Functioning (GAF) and depressive symptoms as measured with the Calgary Depression Scale for Schizophrenia (CDS) will be assessed, in addition to various immunological biomarkers. Secondary outcomes are a 4- and 6-month follow-up assessment of PANSS, BACS, and GAF scores and immunological biomarkers. Additionally, a subgroup of patients will be included in the magnetic resonance imaging (MRI) part of the study where MR spectroscopy and structural, functional, and diffusion MRI will be conducted.

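### The cut from 88 to 69 evaluable patients relies on adjustment for baseline PANSS, which the stated mixed model does not secure

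*Protocol article*

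**What the plan says.** All of this is in the protocol article, section Power calculation and statistical analysis, unless noted.

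- **Starting point.** "A two group *t*-test with a 0.050 two-sided significance level will have 80% power to detect an effect size of 0.610", with 44 patients per arm ("a total sample size of 88; text generated by nQuery Advisor").
- **Reduction.** The article says that "the sample size can be reduced by the data with an Ancova instead of analyzing" by t-test. The size of the cut is tied to the correlation between baseline and follow-up, taken as 0.48 from an earlier trial. This gives 68.7248, and a factor of 1.3 for drop-out brings the total to 90.
- **Analysis actually planned.** A mixed model, not an ANCOVA. The ANCOVA-based number is kept on the argument that "the increase in efficiency compared to the analysis of covariance and therefore the reduction in sample size will not be immense".
- **Covariates.** "As stratification was performed for gender, center, and country, these variables will be used as covariates in the analyses". To these are added any variables found to differ significantly between arms, and the percentage of unused pills.
- **Primary outcome** (Abstract, Methods/design). Symptom severity, "expressed as change in total score on the Positive and Negative Symptom Scale (PANSS) from baseline to end of treatment".

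**The concern.** The factor 1 − r² is the price reduction for conditioning the outcome on its baseline value. The section relies on that reduction and then describes a model whose covariate list leaves out the one variable that produces it. Under the stated rule, baseline PANSS becomes a covariate only if it happens to differ significantly between arms. Under randomisation and a 5% test (the level is my assumption), that happens about one time in twenty, so it is not a planned adjustment.

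The argument that a mixed model is at least as efficient as ANCOVA does not close the gap, because it is true only of some mixed models. One that ignores baseline, analyses plain change, or gives each arm its own baseline mean does not recover the 1 − r² factor. Since the primary outcome is worded as change from baseline, an analyst could reasonably arrive at one of these. What is at stake is roughly 11 to 12 percentage points of power, in a trial whose Discussion expects a negative result as well as a positive one to guide the field.

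**Working it through.** **Inputs from the article:** two-sided α = 0.05; effect size d = 0.61; 1:1 allocation; t-test total 88; r = 0.48; drop-out factor 1.3.

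**Assumption:** d is scaled to the SD of the week-6 score, and baseline and week-6 SDs are equal. The article does not say which SD was used. The reduction formula itself, (1 − r²) × N, is the one that applies relative to a t-test on the follow-up score, which agrees with this reading.

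**1. Reproduce the plan's figures.** Power comes from the non-central t distribution with non-centrality d × √(N/4).
- N = 88: 0.61 × √22 = 2.86, power 80.8%. The smallest group size reaching 80% is 44, as stated.
- ANCOVA step: (1 − 0.48²) × 88 + 1 = 0.7696 × 88 + 1 = 68.7248, as stated.
- Drop-out step: 68.7248 × 1.3 = 89.34, rounded up to 90, as stated.

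The chain of figures is therefore internally correct.

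**2. Variance factor f of the treatment contrast, relative to the week-6 score analysed alone.**
- Baseline as a covariate: 1 − r² = 0.7696.
- Baseline as a repeated response, one mean common to both arms: 0.7696 (generalised least squares with two time points), the same as ANCOVA.
- Baseline not used: 1.00.
- Unadjusted change score: 1 + 1 − 2r = 2(1 − 0.48) = 1.04.
- Baseline as a repeated response with a separate mean per arm: 1.04 for the change contrast and 1.00 for the week-6 contrast, so nothing is gained.

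Because r is below 0.5, subtracting baseline is slightly worse than ignoring it.

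**3. Power at 69 evaluable.** Non-centrality is 0.61 × √(69/4) / √f = 2.53 / √f. Degrees of freedom are 67, or 66 with the baseline covariate.

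| Use of baseline PANSS | f | Non-centrality | Power at 69 | Evaluable N for 80% |
|---|---|---|---|---|
| Covariate, or response with common mean | 0.7696 | 2.89 | 81.2% | 68 |
| Not used | 1.00 | 2.53 | 70.4% | 88 |
| Only subtracted, or separate means with change contrast | 1.04 | 2.48 | 68.7% | 90 |

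The last column is an exact search over equal groups (34, 44 and 45 per arm).

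**4. In randomised patients, by the plan's own factor of 1.3.** 88 × 1.3 = 114.4, so 115; 90 × 1.3 = 117; the plan has 90. Whether 1.3 is the right inflation for 30% drop-out is a separate matter and plays no part here.

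**The case against.** The strongest reply is that the covariate sentence is not a full model statement. It covers several outcomes at once and does not list treatment or visit either, yet nobody would conclude that those are absent. A mixed model with baseline PANSS as a repeated response and a common mean has no baseline covariate, would show exactly this covariate list, and earns the whole 0.7696. The remark that all observations are used, and the comparison with ANCOVA's efficiency, both fit such a model. The article is also condensed, and fuller protocol versions exist that are not shown.

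Much of this stands. A reader might infer that the trial has forfeited its planned power, or that the variance is 35% higher than planned (1.04/0.7696). The document supports neither as a fact. The 35% belongs to one branch only; with baseline unused the ratio is 1.00/0.7696, about 30% higher, and with a common baseline mean there is no loss. Wording the outcome as change from baseline does not by itself specify an unadjusted change-score analysis. If 0.61 were scaled to the SD of change, an unadjusted change-score analysis would need 88 rather than 90. Intermediate visits might recover something when patients drop out, but the article gives no correlations from which to quantify it.

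What does not stand is that this is merely detail left to a fuller document. The article itself states both the reduction and a covariate rule, and the rule does not secure what the reduction needs. Being compatible with a suitable model is not the same as specifying one.

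**Conclusion.** The point holds in conditional form. The reduction from 88 to 69 evaluable depends on conditioning on baseline PANSS; the covariate list omits it; and no other statement fixes its role. If the model uses baseline as a covariate or as a response with a common mean, the planned power is achieved (about 81% at 69 evaluable). Otherwise it is about 69–70%, and 88–90 evaluable are needed for 80%. These figures rest on d = 0.61 in units of the week-6 SD, equal SDs at baseline and week 6, r = 0.48, and 69 patients contributing at week 6. The document does not show that power has been lost; it shows that power has not been secured. That is worth correcting because the correction is so cheap.

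**What to change.** In Power calculation and statistical analysis, state that the primary mixed model includes pre-treatment PANSS total, either as a fixed covariate or as a repeated response with a mean constrained equal across arms, and that the primary contrast is the treatment difference at week 6. Remove any dependence of this adjustment on a test for baseline imbalance. Say also that the screening score serves as the baseline value where the PANSS is not repeated, since the Baseline visit section skips it when screening was less than two weeks earlier. Adjust the other outcomes for their own baseline values in the same way, where these are collected.

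The cost is a sentence or two. No extra data are needed, as a pre-treatment PANSS is already scheduled for every patient. According to Trial status, recruitment in Norway was still open, so the model can be fixed before the final analysis.

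### Beyond four variables that always enter, covariates join the primary and protein-concentration models only if they differ significantly between arms, so selection follows chance imbalance rather than prognosis

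*Protocol article*

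**What the plan says.** All references are to the section on power calculation and statistical analysis in the protocol article, unless stated otherwise.

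- **Baseline comparison.** The arms are tested against each other at baseline ("The baseline characteristics of the prednisolone and placebo group will be compared and tested with a"); continuous characteristics get a t-test, categorical ones a Chi-square test.
- **Clinical models.** A mixed model serves symptom severity, global functioning, depression, cognition and MRI. Gender, center and country enter because they were stratification factors, and percentage of unused pills enters to reflect compliance. Further covariates come in by a rule: "in addition to variables that are significantly different between treatment groups".
- **Protein-concentration model.** The comparison of proteins before and after treatment is "adjusted for covariates significantly differing between the groups".
- **Prediction model.** The association of baseline biomarkers with clinical outcome is assessed in the prednisolone arm only, adjusted for covariates called significant, without a definition.
- **Sensitivity analyses.** Refitting without covariates is planned for the biomarker analysis of covariance models. None is stated for the primary analysis.

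The section gives no list of candidate covariates and no significance threshold for entry. It does not say whether baseline PANSS is in the mixed model.

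**The concern.** Allocation is randomised: "All 90 patients will be randomized 1:1 to either prednisolone or placebo". If randomisation was carried out properly, a significant baseline difference is a chance event. A between-arm test measures imbalance and says nothing about whether a variable predicts the PANSS total score. A variable with little bearing on outcome can enter because it happens to be unbalanced, while a strongly prognostic one that happens to be balanced stays out.

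Two things are at stake. First, the rule can be applied only to data split by treatment group, so the primary model cannot be written down before that split. Second, adjustment for prognostic variables gains precision whether or not they are balanced, and this rule forgoes nearly all of that gain. The trial is small and expects heavy dropout, so the loss matters.

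This is a rule that the text states, not a detail left to an analysis plan. A plan that followed it would inherit the problem.

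**Working it through.** **1. The plan's own figure.** Inputs: "0.050 two-sided significance level"; "80% power to detect an effect size of 0.610 when the sample sizes in the two groups are 44 and 44"; "where a PANSS was performed at baseline and after 6 weeks, r = 0.48 was found"; "Assuming a drop-out rate of 30%, the definitive sample size is calculated at 68.7248 × 1.3 = 89.34224".

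- Two-sample t-test (noncentral t), d = 0.61: 43.2, so 44 per arm and 88 in total. Power at 44 per arm is 0.808.
- ANCOVA reduction: (1 − 0.48²) × 88 + 1 = 0.7696 × 88 + 1 = 68.7248.
- Dropout as the article applies it: 68.7248 × 1.3 = 89.34, so 90.

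The stated 90 reproduces. With 30% dropout, 90 × 0.7 = 63 complete, or about 32 per arm (64), which is used below.

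**2. Chance that the rule alters the model.** For k independent baseline tests at level 0.05, all null by randomisation, P(at least one significant) = 1 − 0.95^k. The article gives neither k nor the level, so both are assumptions.

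| k | 1 − 0.95^k | Expected number entering (0.05k) |
|---|---|---|
| 5 | 23% | 0.25 |
| 10 | 40% | 0.50 |
| 15 | 54% | 0.75 |
| 20 | 64% | 1.00 |

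**3. Chance that a useful covariate enters.** Any one covariate passes with probability equal to the test level, about 5%, however prognostic it is. In 20,000 simulated trials per setting, with one prognostic covariate, it was selected in 4.6% to 5.1% of trials.

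**4. Precision lost.** Assumed: 64 completers, 10 candidates tested, m of them prognostic with r = 0.3 each and mutually independent. With unit outcome variance, adjusting for m such covariates removes m × 0.3² = 0.09m of the residual variance. Against a model that never includes them:

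- Baseline PANSS not in the model (residual variance 1): 0.09/1 = 9% for m = 1; 0.18/1 = 18% for m = 2.
- Baseline PANSS in the model (residual variance 1 − 0.48² = 0.7696): 0.09/0.7696 = 11.7% for m = 1; 0.18/0.7696 = 23.4% for m = 2.

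Simulation of the actual comparison (selection at p < 0.05 among 10 against the same one or two covariates fixed in advance) gives reductions of about 12–18% without baseline PANSS and 13–23% with it. The agreement shows that the rule performs almost as if the covariates were never used. The simulated figures are ratios of squared average standard errors. They also carry the small cost of adding unbalanced covariates, which helps to explain why they can lie slightly above the closed form.

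**5. Type I error.** In the one-covariate simulation, selection gives 0.042 at 32 per arm and 0.046 at 45 per arm, against 0.048 and 0.052 with the covariate always included. With 10 candidates it stays at about 4–5%.

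**The case against.** Several points on the other side stand.

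- **Not every covariate is selected this way.** Gender, center, country and unused pills enter whatever the baseline tests show. The point concerns the additional covariates only.
- **No false-positive inflation.** A reader might infer that choosing the model from the data inflates type I error. The rule is mechanical, and the simulations show it slightly conservative.
- **Baseline PANSS is not shown to be missing.** A reader might infer that it too enters only if unbalanced, and that power at 32 per arm falls to 0.68 instead of 0.78. Those are the simulated values for a single covariate at r = 0.48 under the selection rule and under constant adjustment. The article does not support that reading. It sizes the trial on the baseline correlation, and a mixed model may carry baseline as a covariate or as a repeated outcome. The article does not say which.
- **The prediction model is different.** It uses one arm, so its significant covariates cannot mean a between-arm test. The fault there is an undefined criterion.
- **The biomarker models have a check.** Covariate-free sensitivity analyses would show dependence on selected covariates there. They do not reach the primary analysis.
- **The test is inferred.** The article does not say outright that the t-test and Chi-square results drive selection, but it describes no other between-arm baseline test.

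The defence also notes that r = 0.3 and 10 candidates are not taken from the article. That is correct, and the precision figures are conditional on them.

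**Conclusion.** The point holds for the additional covariates in the clinical mixed model, including the primary PANSS analysis, and in the protein-concentration model. They are chosen on chance imbalance from data split by arm, with no stated candidate list or threshold. At an assumed 0.05 level, a given prognostic variable is used about one time in twenty. The chance that luck alters the model is 40% to 64% for 10 to 20 independent candidates; correlated candidates would change these figures. The avoidable variance is about 12–18% (baseline PANSS not in the model) or 13–23% (in the model) for one or two covariates at r = 0.3, and it scales with the true prognostic strength, which the article does not give.

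The consequence is lost precision and a primary model that is not fixed in advance. Nothing here implies bias, excess false positives or a wrong sample size. The change should be made, but the trial's validity does not depend on it.

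**What to change.** In the power calculation and statistical analysis section, and in any analysis plan derived from it:

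1. Delete the between-arm significance rule from the clinical mixed model and from the protein-concentration model.
2. Fix the covariates before unblinding. Keep the stratification factors already named. State that baseline PANSS is adjusted for, either as a covariate or as a baseline outcome in the mixed model, because the sample size relies on r = 0.48. Add one or two prognostic variables already collected, for example illness duration, chosen on prior grounds.
3. In the one-arm prediction model, replace the undefined criterion with a fixed list of the same kind.
4. Present baseline characteristics descriptively. The p-values do no harm once they no longer drive selection, but they then serve no purpose.

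The cost is wording plus a degree of freedom or two. No new data are needed and the stated 90 does not change. The trial status section reports Norwegian recruitment still open at publication, so the list could be fixed before the codes are broken, provided no unblinded comparison has been made.
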